**Secondary outcomes**

The secondary outcomes will include the following:(1)Radiographic progression assessed at 3, 6, and 12 months using the same classification system(2)Changes in collapse length (mm) measured on serial radiographs at baseline, 3, 6, and 12 months(3)Clinical outcomes, including Harris Hip Score (HHS) and Japanese Orthopaedic Association Hip-Disease Evaluation Questionnaire (JHEQ), evaluated at baseline, 3 months, and 12 months(4)Bone remodeling of the grafted area assessed using computed tomography (CT) before surgery and at 3 and 12 months postoperatively.

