### 2.2. Population

We will include 25 patients with ONFH. As an external control, historical data will be extracted from patients previously diagnosed with ONFH and treated conservatively at Tohoku University Hospital. Eligible patients in the historical cohort must meet the following criteria: (1) diagnosis of ONFH based on radiographic and MRI findings at the time of initial presentation; (2) classification as Stage 1, 2, 3A, or 3B (excluding Stage 4) and Type B, C1, or C2 according to the criteria of the Japanese Investigation Committee (JIC) of Idiopathic Osteonecrosis of the Femoral Head [40]; (3) age ≥ 18 years at the time of diagnosis; and (4) no restriction on sex [41]. Eligible patients in the historical cohort will be selected to match the study population as closely as possible. Historical control data will be extracted from patients treated conservatively at Tohoku University Hospital between Jun 2005 and May 2021. During this period, radiographic and MRI-based diagnosis and staging were performed according to the Japanese Investigation Committee classification. Nevertheless, temporal changes in clinical practice and patient management may have influenced the outcomes and should be considered when interpreting the results.

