### 2.8. The Study Procedure and Schedule

The study procedures and schedule are summarized in Table 1, in accordance with the SPIRIT recommendations. Eligible patients will be identified during outpatient visits. After a detailed explanation of the study, written informed consent will be obtained. Participants may withdraw their consent at any time without any consequences. Following consent, screening assessments will be performed within 1 month prior to surgery. Baseline data, including demographic characteristics (age, sex, height, and weight), medical history, and comorbidities, will be collected from medical records. Eligibility will be confirmed, and patient registration will be completed before surgery. All enrolled patients will undergo the surgical procedure as described above. Postoperative follow-up assessments will be conducted at 1 week, 4 weeks, 3 months, 6 months, and 12 months after surgery. Radiographic evaluation using X-rays will be performed at baseline and at each follow-up visit. Computed tomography (CT) will be performed at baseline and during follow-up to assess bone remodeling. Clinical laboratory tests will be conducted at baseline and during the early postoperative period. Vital signs, including blood pressure, pulse rate, body temperature, and respiratory rate, will be monitored during hospitalization and the immediate postoperative period. Patient-reported outcomes, including the HHS [42] and JHEQ [43], will be assessed at baseline, 3 months, and 12 months. Adverse events will be monitored throughout the study period regardless of their causal relationship with the intervention. Rehabilitation will be initiated during hospitalization and continued after discharge according to the patient’s weight-bearing status. Postoperative rehabilitation will generally be performed once daily during hospitalization and approximately once weekly until 6 weeks after surgery, with further adjustments as clinically indicated. Patients will remain non-weight-bearing for 3 weeks after surgery, followed by gradual progression to weight-bearing according to clinical symptoms and radiographic findings. Information on concomitant medications, including corticosteroids, immunosuppressive agents, and osteoporosis treatments, will be collected from baseline until the end of follow-up.

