Continuous variables will be expressed as mean ± standard deviation or median (interquartile range), as appropriate, and categorical variables as frequencies and percentages. The primary outcome (progression of ONFH within 1 year) will be compared between the intervention group and the historical control group. To reduce confounding due to the non-randomized design, propensity score matching will be performed. The propensity score will be estimated using a logistic regression model including age, sex, body mass index, disease stage, disease type, and etiology of ONFH. Information regarding corticosteroid use, alcohol consumption, concomitant medications, and year of diagnosis will also be collected. Because of the limited sample size and exploratory nature of this pilot study, these variables will not be included in the primary propensity score model to avoid overfitting but will be described and considered when interpreting the results. Patients will be matched 1:1 using nearest-neighbor matching with a caliper width of 0.2 times the standard deviation of the propensity score. Patients for whom an adequate match cannot be identified will be excluded from the matched analysis. This may reduce the effective sample size and limit the generalizability of the findings. Covariate balance after matching will be assessed using standardized mean differences, with values < 0.1 indicating adequate balance. After matching, paired categorical variables, including the primary outcome, will be analyzed using McNemar’s test. Secondary outcomes will be analyzed descriptively and compared between groups using appropriate statistical methods. Missing data will be handled using complete case analysis. Because the historical control cohort is derived from institutional databases with routinely collected clinical and imaging records, the amount of missing data is expected to be minimal. Therefore, complete case analysis was considered appropriate for this exploratory study. Because the amount of missing data is expected to be minimal, formal sensitivity analyses or multiple imputation procedures are not planned. Alternative approaches to missing data will be considered in future confirmatory studies if necessary. All statistical analyses will be performed using JMP version 19.0 (SAS Institute, Cary, NC, USA). A two-sided *p*-value < 0.05 will be considered statistically significant.

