This study has several strengths. It evaluates a novel combined technique that addresses both intraosseous and intra-articular pathology. In addition, the externally controlled design with propensity score matching allows for adjustment of baseline differences between groups, improving the validity of comparisons. Furthermore, both radiographic and clinical outcomes are assessed, enabling a comprehensive evaluation of treatment effectiveness. However, several limitations should be acknowledged. First, this is a single-center study with a relatively small sample size, as this trial was designed as a pilot study, which may limit generalizability. Second, the use of a historical control group introduces potential selection bias and residual confounding, despite statistical adjustment. In particular, differences in treatment indications and clinical practice over time may have influenced the outcomes. Baseline is defined as the time of surgery in the intervention group and the time of initial diagnosis in the historical control group. This asymmetry may introduce bias because disease progression occurring before surgery in the intervention group is not captured. Furthermore, residual confounding due to unmeasured factors, including corticosteroid use, alcohol consumption, symptom duration, and temporal changes in clinical practice, cannot be completely excluded. In addition, baseline patient-reported outcome measures, including the HHS and JHEQ, are not available for the historical control cohort. Therefore, these outcomes will be evaluated descriptively within the intervention group, and direct comparisons between groups will not be possible. Third, the follow-up period is limited to short-term outcomes, and long-term durability, including prevention of femoral head collapse and conversion to total hip arthroplasty, remains unclear. In addition, the collapse length measurement used in this study has not been formally validated, and intra- and inter-observer reliability were not assessed. Therefore, measurement variability may influence the reproducibility of radiographic outcomes. Finally, variability in surgical technique and patient characteristics may influence the results. Therefore, caution is required when generalizing the findings to other populations and clinical settings. In conclusion, this study is expected to provide important preliminary evidence regarding the feasibility and potential effectiveness of arthroscopy-assisted core decompression combined with OCP/Gel implantation. The findings may contribute to the development of improved joint-preserving strategies for ONFH and support future large-scale prospective studies. This approach may offer a practical and scalable alternative to more complex regenerative therapies.

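### The 3- and 6-month radiographic comparison sets scheduled films in the operated arm against unscheduled control films, so it is unreliable in a direction the protocol cannot determine

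*Protocol article*

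**What the plan says.** Section 2.6 of the protocol article names two radiographic secondary outcomes with interim time points: "Radiographic progression assessed at 3, 6, and 12 months using the same classification system" and "Changes in collapse length (mm) measured on serial radiographs at baseline, 3, 6, and 12 months". Neither is restricted to the intervention arm.

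Section 2.10 then states: "Secondary outcomes will be analyzed descriptively and compared between groups using appropriate statistical methods". The same section sets a two-sided 0.05 threshold, handles missing data by complete case analysis and plans no sensitivity analysis, because little missing data is expected.

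The Discussion takes one pair of secondary outcomes out of the comparison. HHS and JHEQ have no baseline in the historical cohort, so "these outcomes will be evaluated descriptively within the intervention group, and direct comparisons between groups will not be possible". Nothing similar is said of the radiographic outcomes.

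The imaging schedule belongs to the operated patients. Section 2.8 says "Postoperative follow-up assessments will be conducted at 1 week, 4 weeks, 3 months, 6 months, and 12 months after surgery" and "Radiographic evaluation using X-rays will be performed at baseline and at each follow-up visit". Table 1 gives the 3-month, 6-month and 1-year visits a window of ±2 weeks.

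Of the controls, section 2.2 says "Historical control data will be extracted from patients treated conservatively at Tohoku University Hospital between Jun 2005 and May 2021", and section 2.10 that "the historical control cohort is derived from institutional databases with routinely collected clinical and imaging records". No imaging interval, film window or requirement for an interim film is given for them.

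**The concern.** One arm is filmed by schedule. The other is filmed when routine care produced a film, and complete case analysis keeps only those who were filmed. If having a film near 3 or 6 months is related to progression, the retained controls are a selected sample, and a difference between arms can appear, or be hidden, without any treatment effect.

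The article justifies its missing-data approach by the routine nature of the control records. Routine collection shows that films were taken, but not that they were taken at 3 and 6 months after diagnosis. The Discussion lists other asymmetries between the arms (time zero, era, unmeasured confounders) but not this one.

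At stake is the early time course of progression and collapse. These are secondary outcomes of a pilot, but section 2.10 says its estimates of progression and effect size will inform later sample sizes, so a distorted early effect could be carried forward.

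**Working it through.** **Which outcomes the between-group sentence covers.** Section 2.6 lists four secondary outcomes.

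| Secondary outcome | Can it be compared between groups? |
|---|---|
| Radiographic progression at 3, 6, 12 months | Not withdrawn anywhere |
| Change in collapse length to 3, 6, 12 months | Not withdrawn anywhere |
| HHS and JHEQ | No, withdrawn in the Discussion |
| CT remodeling of the grafted area | No, controls have no graft |

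The two radiographic outcomes are all that the sentence in 2.10 can refer to, and both include 3 and 6 months.

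**Is there a figure to reproduce?** No. The article gives no expected early progression rate and no film availability for controls, and the 25 patients do not come from a power calculation.

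**Effect of selective filming.** The following are assumptions, not figures from the article:
- p = true control progression at the time point
- a = chance of a film if the hip has progressed
- b = chance of a film if it has not

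Observed progression among filmed controls = p·a / (p·a + (1 − p)·b)

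Expected filmed controls, if all 25 patients are matched = 25 × (p·a + (1 − p)·b)

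With p = 0.20:

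| Filming pattern | a | b | Observed progression | Bias (points) | Filmed, of 25 |
|---|---|---|---|---|---|
| Unrelated to progression | 0.60 | 0.60 | 0.12/0.60 = 20.0% | 0 | 15.0 |
| More often in progressors | 0.90 | 0.60 | 0.18/0.66 = 27.3% | +7.3 | 16.5 |
| Strongly symptom-driven | 0.90 | 0.30 | 0.18/0.42 = 42.9% | +22.9 | 10.5 |
| Less often in progressors | 0.60 | 0.90 | 0.12/0.84 = 14.3% | −5.7 | 21.0 |

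If a missing film were instead read as no progression, observed progression would be p·a = 0.20 × 0.60 = 12%, again an understatement.

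**Wider range.** With p from 10% to 40% and the same kinds of filming pattern, the extremes are both at p = 0.40:
- a = 0.90, b = 0.30: 0.36/0.54 = 66.7%, bias +26.7 points
- a = 0.50, b = 0.80: 0.20/0.68 = 29.4%, bias −10.6 points

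**Why either sign is possible.** The Introduction says patients are often symptom-free before collapse and have pain after it, which makes symptom-driven films plausible. Against that, THA is an event in the primary outcome but is not named in the secondary radiographic outcome. A control converted to THA before 6 months has no native femoral head to film at 6 months, so complete case analysis can drop some of the worst controls.

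**Loss of pairs.** Section 2.10 matches 1:1 and assigns McNemar's test to paired categorical variables. A control without a film removes its whole pair. Even with filming unrelated to progression, 60% availability leaves 15 of 25 pairs, and the covariate balance achieved by matching need not hold in them.

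The calculation covers progression only. No size is given for collapse length, although the same selection applies to it.

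**The case against.** The strongest reply is that the article never says control films at 3 and 6 months are lacking. It expects little missing data, and a condensed article may leave control film windows to the full protocol. This stands as far as it goes. A reader might infer that controls had no visits at those times; the article supports only that no protocol visit or film is set for them.

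Second, a reader might infer that the comparison must favour the operation. The article does not say what prompted control films, and the working shows that the bias can be zero or reversed. This stands too: overstatement of control progression is plausible but not established.

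Third, if stage does not regress, a later film without progression also settles 6 months. The article neither states nor excludes such a rule. It would recover some controls, but it would not date progression first seen on a later film.

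Fourth, the 1-year control film is equally unscheduled, so 3 and 6 months cannot be called unsound and 1 year sound on that ground alone. This is correct and is reflected in the fix.

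Fifth, the sentence in 2.10 is generic, the outcomes are secondary, and the article already warns of selection bias and confounding. That limits the importance of the point. It does not remove it, because the sentence has nothing but the radiographic outcomes to apply to, and the general warnings do not mention unequal imaging.

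**Conclusion.** The point holds in a limited form. As written, the plan compares 3- and 6-month progression and collapse length between an arm with scheduled films and a control group whose values depend on unscheduled routine films, with complete case handling and no sensitivity analysis. At a true 20%, observed control progression could be 27% to 43% if progressors were filmed more often, or about 14% if they were filmed less often. Across the assumed ranges the bias runs from about −11 to +27 percentage points. All filming probabilities and progression rates are assumptions, and the bias is zero if filming is unrelated to progression.

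The conclusion does not depend on the sign: the early comparison cannot be interpreted either way. It should be changed, but it concerns secondary outcomes of an exploratory pilot. The 1-year comparison shares the weakness of unscheduled control films and needs its own safeguard.

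**What to change.** In sections 2.6 and 2.10:

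- Report radiographic progression and collapse length at 3 and 6 months descriptively within the intervention arm, as the Discussion already does for HHS and JHEQ.
- Limit the between-group radiographic comparison to 1 year. State a film window around 1 year for controls and report how many matched controls have a film within it.
- If any 3- or 6-month control data are shown, label them descriptive, give a stated window and the number of controls available, and attach no p-value.

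This is a change of wording, plus a count of control films. The downside is that the early between-group comparison is given up.

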### 2.7. Data Collection

All data will be recorded electronically using standardized case report forms. The case report forms will include demographic data (age and sex), underlying conditions associated with ONFH, medication history, and medical history. In addition, data obtained during eligibility assessment will be collected, including clinical laboratory tests and imaging findings (X-ray and CT). These data will be used to assess baseline characteristics, clinical outcomes, and safety. Data accuracy will be ensured through regular monitoring and verification by the study investigators (Table 1).

### 2.8. The Study Procedure and Schedule

The study procedures and schedule are summarized in Table 1, in accordance with the SPIRIT recommendations. Eligible patients will be identified during outpatient visits. After a detailed explanation of the study, written informed consent will be obtained. Participants may withdraw their consent at any time without any consequences. Following consent, screening assessments will be performed within 1 month prior to surgery. Baseline data, including demographic characteristics (age, sex, height, and weight), medical history, and comorbidities, will be collected from medical records. Eligibility will be confirmed, and patient registration will be completed before surgery. All enrolled patients will undergo the surgical procedure as described above. Postoperative follow-up assessments will be conducted at 1 week, 4 weeks, 3 months, 6 months, and 12 months after surgery. Radiographic evaluation using X-rays will be performed at baseline and at each follow-up visit. Computed tomography (CT) will be performed at baseline and during follow-up to assess bone remodeling. Clinical laboratory tests will be conducted at baseline and during the early postoperative period. Vital signs, including blood pressure, pulse rate, body temperature, and respiratory rate, will be monitored during hospitalization and the immediate postoperative period. Patient-reported outcomes, including the HHS [42] and JHEQ [43], will be assessed at baseline, 3 months, and 12 months. Adverse events will be monitored throughout the study period regardless of their causal relationship with the intervention. Rehabilitation will be initiated during hospitalization and continued after discharge according to the patient’s weight-bearing status. Postoperative rehabilitation will generally be performed once daily during hospitalization and approximately once weekly until 6 weeks after surgery, with further adjustments as clinically indicated. Patients will remain non-weight-bearing for 3 weeks after surgery, followed by gradual progression to weight-bearing according to clinical symptoms and radiographic findings. Information on concomitant medications, including corticosteroids, immunosuppressive agents, and osteoporosis treatments, will be collected from baseline until the end of follow-up.

### 2.9. Data Management

All data will be collected and recorded using standardized electronic case report forms. Data entry will be performed by trained investigators and verified to ensure accuracy and completeness. Data quality will be maintained through regular monitoring and validation procedures. All patient information will be anonymized prior to analysis to ensure confidentiality. Access to the study database will be restricted to authorized study personnel only.

### 2.10. Statistical Analysis

As this study is designed as a pilot exploratory trial, a formal sample size calculation based on power analysis was not performed. A target sample size of 25 patients was determined based on the following considerations: (1) the rarity of ONFH, with an estimated annual incidence of approximately 2200 cases in Japan; (2) the novel nature of the intervention, for which no prior data are available to estimate effect size; and (3) the general recommendation that pilot studies should enroll at least 25 participants to provide a preliminary estimate of the effect size with sufficient precision for planning future confirmatory trials [44]. The findings of this study are intended to inform the design of future large-scale trials. Previous studies have reported that the progression rate of conservatively managed ONFH varies depending on disease stage and lesion size. The present pilot study is intended to provide preliminary estimates of progression rates and effect sizes, which will be used to inform sample size calculations for future confirmatory studies.

Continuous variables will be expressed as mean ± standard deviation or median (interquartile range), as appropriate, and categorical variables as frequencies and percentages. The primary outcome (progression of ONFH within 1 year) will be compared between the intervention group and the historical control group. To reduce confounding due to the non-randomized design, propensity score matching will be performed. The propensity score will be estimated using a logistic regression model including age, sex, body mass index, disease stage, disease type, and etiology of ONFH. Information regarding corticosteroid use, alcohol consumption, concomitant medications, and year of diagnosis will also be collected. Because of the limited sample size and exploratory nature of this pilot study, these variables will not be included in the primary propensity score model to avoid overfitting but will be described and considered when interpreting the results. Patients will be matched 1:1 using nearest-neighbor matching with a caliper width of 0.2 times the standard deviation of the propensity score. Patients for whom an adequate match cannot be identified will be excluded from the matched analysis. This may reduce the effective sample size and limit the generalizability of the findings. Covariate balance after matching will be assessed using standardized mean differences, with values < 0.1 indicating adequate balance. After matching, paired categorical variables, including the primary outcome, will be analyzed using McNemar’s test. Secondary outcomes will be analyzed descriptively and compared between groups using appropriate statistical methods. Missing data will be handled using complete case analysis. Because the historical control cohort is derived from institutional databases with routinely collected clinical and imaging records, the amount of missing data is expected to be minimal. Therefore, complete case analysis was considered appropriate for this exploratory study. Because the amount of missing data is expected to be minimal, formal sensitivity analyses or multiple imputation procedures are not planned. Alternative approaches to missing data will be considered in future confirmatory studies if necessary. All statistical analyses will be performed using JMP version 19.0 (SAS Institute, Cary, NC, USA). A two-sided *p*-value < 0.05 will be considered statistically significant.

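### The pilot is meant to supply an effect size, but its primary comparison is fixed as a McNemar test in a matched set that may fall below 25 pairs, will probably miss the plan's own balance standard, and cannot support the precision claimed

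*Protocol article*

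**What the plan says.** All of this stands in section 2.10 (Statistical Analysis) of the protocol article.

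- **Sample size.** The plan states openly that "a formal sample size calculation based on power analysis was not performed". The target of 25 rests on the rarity of the disease, the lack of prior data, and a cited recommendation that "pilot studies should enroll at least 25 participants to provide a preliminary estimate of the effect size with sufficient precision".
- **Purpose.** The same paragraph says the pilot should yield preliminary progression rates and effect sizes, from which later confirmatory studies will be sized.
- **Matching.** A logistic propensity model uses age, sex, BMI, stage, type and etiology. Then "Patients will be matched 1:1 using nearest-neighbor matching with a caliper width of 0.2 times the standard deviation of the propensity score". Anyone left without a partner inside the caliper drops out of this analysis, and the plan acknowledges that this may shrink the sample.
- **Balance.** Standardized mean differences (SMDs) are computed after matching, "with values < 0.1 indicating adequate balance". No consequence is attached to a larger value.
- **Primary analysis.** After matching, "paired categorical variables, including the primary outcome, will be analyzed using" McNemar's test, with significance at two-sided p < 0.05. Missing data are handled by complete cases.

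The number of historical controls is not given. Section 2.2 says only that they were treated conservatively at the same hospital between June 2005 and May 2021.

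**The concern.** The stated purpose and the stated analysis do not meet. A trial that sizes its successor needs a between-group difference and its uncertainty. McNemar's test gives a p-value that depends only on the discordant pairs, and the plan names no effect measure or interval to go with it.

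Three further features weaken the matched comparison:

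1. The reason given for 25 is the precision of the effect estimate. That precision depends on the pairs analysed, not on the patients enrolled, and nothing is added for patients lost to the caliper or to missing outcomes.
2. An SMD limit of 0.1 is below the chance variation of an SMD in groups of 25, so a perfectly sound match will usually fail it.
3. The interval that 25 pairs can give is wide compared with any difference the next trial might be designed around.

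At stake is whether the pilot delivers its planned output. Readers could be left with a p-value from a set that the plan's own standard labels inadequately balanced.

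**Working it through.** The figure of 25 comes from a rule of thumb without formula inputs, so there is nothing to reproduce. Three consequences of the plan can be checked. Control-pool size, baseline differences, category frequencies and progression rates are not in the documents and are assumed below.

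**1. Pairs left after matching.** Simulation with 600 runs per cell: 25 treated patients, a logistic propensity score on the six covariates, and greedy 1:1 matching without replacement. The caliper is 0.2 SD on the propensity scale, as written.

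| Assumed control pool | Mean pairs, no baseline difference | P(<25 pairs) | Mean pairs, 0.6 SD shift | P(<25 pairs) |
|---|---|---|---|---|
| 50 | 19.6 | 1.00 | 15.1 | 1.00 |
| 100 | 22.9 | 0.85 | 19.0 | 1.00 |
| 200 | 24.0 | 0.60 | 21.3 | 0.96 |
| 400 | 24.5 | 0.34 | 22.4 | 0.90 |

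With the caliper on the logit scale, no shift and 400 controls, P(<25) falls to 0.13. Complete-case handling can remove further pairs, because a missing outcome in either member loses the pair.

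**2. The balance standard.** With n per group, the standard error of an SMD under chance balance is about √(2/n). For n = 25 this is √0.08 = 0.283, so

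P(|SMD| < 0.1) = 2Φ(0.1/0.283) − 1 = 0.276.

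For six independent covariates, 0.276⁶ ≈ 0.0004. Matching improves on pure chance, but not by enough: all six covariates met the limit in 0 to 2.5% of simulated runs in every scenario, and in 0 to 0.3% when each category level was checked separately. For a category holding 10% of patients, a difference of one patient in 25 gives 0.04/√(0.1 × 0.9) = 0.04/0.30 = 0.13, already above the limit. For a 50% category, two patients give 0.08/0.50 = 0.16.

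**3. Precision of the risk difference.** Let p₁₀ and p₀₁ be the two discordant-pair probabilities. The half-width is

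1.96 × √[(p₁₀ + p₀₁ − (p₁₀ − p₀₁)²)/n].

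Outcomes within a pair are taken as independent. Positive correlation would narrow the interval.

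| Assumed progression, control vs treated | p₁₀, p₀₁ | 25 pairs | 20 pairs |
|---|---|---|---|
| 50% vs 25% | 0.375, 0.125 | 1.96√(0.4375/25) = 0.26 | 0.29 |
| 50% vs 30% | 0.35, 0.15 | 1.96√(0.46/25) = 0.27 | 0.30 |
| 60% vs 20% | 0.48, 0.08 | 1.96√(0.40/25) = 0.25 | 0.28 |

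In the first two rows the half-width exceeds the assumed difference itself (25 and 20 points).

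**What the test alone conveys.** With 5 discordant pairs the smallest exact two-sided p is 2 × 0.5⁵ = 0.0625; with 6 it is 2 × 0.5⁶ = 0.031. Significance therefore needs at least 6 discordant pairs, and with exactly 6 all must point the same way. A p-value from so few pairs says little about the size of the effect.

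**The case against.** The strongest reply is that this is a declared exploratory pilot, written up as a condensed article, and that several sharper readings do not hold.

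- *The analysis will fall below the 25 the plan needs.* A reader might infer this, but the recommendation concerns enrolment, the pool size is unstated, and a large, similar pool often matches all 25. The plan also discloses the possible loss. What stands is that 25 has no allowance for it.
- *The plan yields a p-value in place of any estimate.* This is too strong. Categorical variables are to be summarized as counts and percentages, so a crude difference could be read off, and a separate analysis plan could add an interval. What stands is that the article fixes the primary comparison as a test and names no effect measure, although effect sizes are its stated aim.
- *The propensity model is overfitted with about ten parameters.* That assumes dummy coding and three etiology levels. The plan lists six covariates and gives no coding, so this is not established.
- *The test is unadjusted.* It is not, since matching is the adjustment. The 0.1 limit is also a descriptive label and does not gate the analysis. What stands is that the label will almost always read unfavourably.
- *Power is too low.* No power is claimed, and power depends on the assumed rates. With 25 pairs, exact McNemar power is 0.32 at 50% vs 25% but 0.75 at 60% vs 20%. Low power is not a fault here.
- *The precision wording reports a cited recommendation.* True, but the plan adopts it as a reason for 25, so it should fit the analysis planned.

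**Conclusion.** The point holds and should be fixed; it does not invalidate the design. The article gives estimation as the pilot's purpose but fixes its primary comparison as a test with no effect measure or interval. This mismatch rests on the text alone.

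The sizes rest on assumptions. The matched set may well be smaller than 25: about 20, 23 or 24 pairs with 50, 100 or 200 similar controls, and fewer if the groups differ at baseline. Meeting the 0.1 limit on every covariate is very unlikely in all scenarios tried (0 to 2.5%), so the comparison will probably be made in a set that the plan's own standard calls inadequately balanced. A half-width of 25 to 27 points with 25 pairs, or 28 to 30 with 20, does not support the claim that 25 patients suffice "to provide a preliminary estimate of the effect size with sufficient precision for planning future confirmatory trials".

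The documents do not show that fewer than 25 pairs is certain, that the propensity model is overfitted, or that matching with McNemar's test is an invalid paired analysis.

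**What to change.** 1. Make the primary result the paired risk difference in 1-year progression with a 95% CI, accompanied by an exact or mid-p McNemar test.
2. Report the progression rate in all 25 treated patients, matched or not, with an exact CI. This estimate does not depend on the control pool.
3. Add a sensitivity analysis for residual imbalance: a propensity-weighted risk difference (for example with overlap weights) using all treated patients and all eligible controls, with sparse stage, type and etiology levels collapsed.
4. Replace the precision claim with the expected half-width: about ±25 to 27 points with 25 pairs and ±28 to 30 with 20, with the assumed rates stated.

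**Cost.** Wording, a little more analysis work, and a less favourable stated precision. Overlap weights balance only the modelled terms and target a slightly different population, which is why they belong in a sensitivity analysis. They help but do not cure the imprecision. In a simulation with 150 assumed controls, the standard error of the risk difference fell from 0.133–0.146 with matching to 0.101–0.110, so the half-width falls from about 26–29 points to 1.96 × 0.101 to 1.96 × 0.110, or 20–22 points.
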